### 5.6.1 Body Composition Assessment

The first component of each assessment to be completed is the Body Composition Assessment. The Body Composition Assessment is to be completed at the Body Composition Laboratory at the Royal Children’s Hospital. A laboratory technician, with the appropriate accreditation will conduct the assessment (appendix g).

The following data will be collected:

- Self-reported pre-diagnosis weight
- Height (stadiometer)
- Weight (digital scales)
- Waist circumference (non-expandable tape at top of iliac crest)
- Hip circumference (non-expandable tape at widest point of the buttocks)
- Blood pressure (Omron T8)
- Whole-body and segmental body composition - fat mass, fat-free mass (Lunar Prodigy DEXA scanner)
- Bone mineral density – hip and lumbar spine (Lunar Prodigy DEXA scanner)
- Physical functioning – hand grip strength (Smedley handheld dynamometer); timed chair stands (5 sit-to-stand repetitions)

At this assessment, participants will be provided with the pathology request form for the blood sample collection and two 5ml SST tubes to take with them to the Sullivan Nicholaides Pathology (SNP) Collection Centre, the activity monitor pack (including the hip and thigh monitors and express postage return pack), a food model booklet for use in the telephone interviews and the self-report questionnaire (with reply-paid envelope).

Body composition and bone mineral density will be measured by a DEXA machine. Having a DEXA scan done is similar to having an x-ray but has about 10% of the radiation of a chest x-ray.

### 5.6.2 Blood Sample Collection

Participants are given a Sullivan Nicolaides Pathology (SNP) request form to have 18ml of blood taken at their nearest Collection Centre within 2-3 days. Participants are instructed to fast for a minimum of 10 hours prior to having the sample taken.

Blood will be collected using standard aseptic procedures by trained phlebotomists. Samples will be spun at the SNP Collection Centre and then couriered to the SNP head office in Taringa, Brisbane. Some analysis will be performed on the fresh sample at SNP Pathology, including glucose, HbA1c, triglycerides and cholesterol profile. A 9ml sample will be couriered to the Princess Alexandra Hospital (PAH) Chemical Pathology where the sample will be centrifuged and the plasma, buffy coat and red blood cells aliquoted for freezing. The samples will be treated under usual strict temperature and blood handling procedures by trained chemical pathologists and kept in a secure area of the hospital. Members of the research team will collect the frozen samples from pathology on a weekly basis for longer-term storage in -80^o^c freezers on-site at the PAH. These freezers are kept in a secure area and accessible only to authorized staff.

Planned assays for metabolic biomarkers (insulin, leptin, adiponectin [total and high molecular weight], CRP [total and high sensitivity]) will be conducted by Mater Pathology and collaborators at Mater Medical Research Institute. Genomic and DNA methylation-based biomarkers will be assayed by collaborators at the Institute of Health and Biomedical Innovation at QUT.

### 5.6.3 Physical Activity Measurement

Participants are asked to wear a Thigh Monitor (activPAL3 inclinometer) and a Hip Monitor (Actigraph GT3X+ accelerometer) for 7 consecutive days. The activPAL3 is a small, lightweight and unobtrusive device worn on the front of the right thigh, about a third of the way between the top of the thigh and the knee, attached with an adhesive patch (Hypafix). The device is waterproofed by placing it in a nitrile finger cot and wrapping it in Tegaderm transparent film. The activPAL3 is worn continuously for the 7 days (i.e. during waking and sleeping hours). It records body posture and activity by monitoring the position of a person’s lower limb, and gives information on time spent sitting/reclining, standing and stepping as well transitions from sitting to standing. The GT3X+ accelerometer is a small, lightweight and unobtrusive device, worn on the right hip on an adjustable belt that records the time, duration and frequency of walking or running movements. The GT3X+ is worn during waking hours only and is removed for any water activities (showering, bathing, swimming etc.). During the 7 days the monitor is worn, participants complete a diary to record sleep time, the time the hip monitor is put on and removed for the day and within-day removal times for both the hip and thigh monitor.

### 5.6.4 Telephone Interviews

The telephone interview component consists of two unscheduled telephone interviews with participants (appendix h). The first telephone interview collects self-reported data on:

- physical activity levels - Active Australia Survey (eight items + two additional items on strength exercise)
- dietary intake – 24 hour dietary recall; fruit and vegetable intake; breakfast consumption (two items); perceived deprivation (two items)
- breast cancer related information – menopausal status at diagnosis; treatments received and date completed; reconstruction surgery; lymphoedema; Breast Cancer Network Australia (BCNA) membership
- demographic and health characteristics – age; employment status; educational level; income; marital status; ethnicity; smoking status; co-morbidities; use of blood pressure, lipid lowering and diabetes medications

The second telephone interview includes a second 24-hour dietary recall and the two perceived deprivation items. The two 24-hour dietary recalls should capture one week day and one weekend day.

The 24 hour dietary recalls are conducting using FoodWorks Interview Software, developed by Xyris Software, Brisbane, which uses the multi-pass method for recalling all foods and drinks consumed. Participants use the food model booklet provided to assist in estimating portion sizes.

During the final telephone interview for the study (at 18-months), participants will be asked if they give their consent to be recontacted in the future to see if they would be interested in continuing their participation in research in this area, should funding become available. They are only asked to provide consent to be contacted. If and when participants are contacted, they will be informed what would be involved in continuing participation and asked whether they choose to participate.

### 5.6.5 Questionnaire

The self-administered questionnaire collects information on patient reported outcomes (quality of life, fatigue, body image, menopausal symptoms, fear of cancer recurrence, arthralgia, peripheral neuropathy) and a range of constructs related to social-cognitive theory as well as sleep and depression, which will be examined to assess whether they mediate or moderate the relationship between the intervention and the primary and secondary outcomes (appendix i). The specific instruments included in the questionnaire are (version 3, amended 20/08/13):

- Outcome Expectancy for diet and physical activity – Diet items modified from Zunft et al., 1997; PA developed based on Rodgers & Brawley, 1991 & Williams et al., 2005
- Satisfaction with diet and physical activity outcomes – Developed for study based on outcome expectancy items
- Self-regulation for diet and physical activity – Modified from Petosa, 1993
- Self-efficacy for diet and physical activity – Diet modified Linde Barriers-based Self-Efficacy (for diet & PA) scale; PA modified Marcus et al., 1992
- Social support – Sallis Social Support for Eating & Exercise scales
- Perceived environmental opportunity for healthy eating and physical activity – Healthy eating modelled from Disdall et al., 2005 & Moore et al., 2008; Physical activity modified IPS-E, Inoue et al., 2008
- Sleep disturbance – Insomnia Severity Index (Q1-5)
- Quality of life – PROMIS Global Health Scale
- Fatigue – FACT-IT
- Depression – PROMIS SF-Depression 1.0
- Body image – PAL Relationships and Body Image Scale
- Menopausal symptoms – Greene Climacteric Scale
- Fear of cancer recurrence – Concerns about Recurrence Questionnaire (CARQ-4)
- Arthralgia (Breast Cancer Prevention Trial Musculoskeletal Pain Subscale)
- Peripheral neuropathy (Patient Neurotoxicity Questionnaire (PNQ))

The questionnaire is available for completion in either hard-copy (given to all participants attending for their Body Composition Assessment) or electronic format (LimeSurvey platform, hosted on the Faculty of Health Sciences secure server).

All intervention participants will also be given a short satisfaction questionnaire to complete at the end of the program (after 12-months) (appendix j). This questionnaire will ask about their overall satisfaction with the program, satisfaction with particular components, areas of participation they found difficult and suggestions for improvements to the program.

### 5.6.6 Clinical and treatment information

Clinical details including tumour size, type and histological grade, surgery details, lymph node involvement and hormonal status will be abstracted from pathology records, held at the Queensland Cancer Registry. A project officer will work on-site at the Queensland Cancer Registry to obtain this data from the Queensland Health electronic records database.

Participants will provide consent for treatment information (chemotherapy and/or radiotherapy cycle, agents etc.) to be collected from hospital medical records. This data will collected by a member of the research team following recruitment of all participants from each hospital. Collection of this data will be dependent on adequate resources for study staff to abstract this data from hospital medical records.

# Safety reporting

Adverse events (AEs) will be assessed for all participants at each follow-up assessment (6-, 12- and 18-month). In addition, all participants will specifically be asked about unintended weight loss (i.e. weight loss greater than expected based on changes made to physical activity and dietary intake). All AEs will be recorded on a standard Adverse Event Report Form (appendix k) and submitted to the chief investigator.

The chief investigator will determine the severity and relationship of the AE to the intervention and take appropriate action(s). Severity will be graded from 1 (mild) to 5 (fatal) based on the National Cancer Institute’s Common Terminology Criteria for Adverse Events (CTCAE) classification. The attribution of the AE to the intervention will be determined to be unrelated (unrelated or unlikely) or related (possible, probable or definite). AE Report Forms for participants reporting unintended weight loss will be reviewed by the CI in consultation with CI [name] (Medical Oncologist) to determine the appropriate course of action. The chief investigator will submit AE Report Forms to the Safety Monitoring Committee, which will oversee the monitoring of trial safety and AEs reporting for the study. The Committee will consist of three members including a cancer clinician and two behavioural scientists. The Chair of the committee will have appropriate experience or training in trial safety. All AEs will be reported to the chair of the committee, with serious AEs that may be related to the intervention reported within 48 hours of notification. The committee will meet via teleconference as needed.

# Outcomes/ Measures

## Primary outcome

- Weight loss (% initial body weight)

## Secondary outcomes

- Physical activity
- Dietary intake
- Waist and hip circumference
- Body composition and bone mineral density
- Blood pressure
- Clinical biomarkers of metabolic health: glucose, lipids, HbA1c, insulin, leptin, adiponectin, C Reactive Protein
- Genomic and DNA Methylation-based biomarkers
- Patient-reported outcomes: quality of life, fatigue, body image, menopausal symptoms, fear of cancer recurrence
- Cost-effectiveness

# Statistical methods

## Sample size and justification

### Power for primary endpoints

The sample size calculation is based on observing an average weight loss in the intervention group at the end of the intervention (12-months) of 7% of initial body weight[[30](#_ENREF_30)] and allowing for a small regain in weight in the intervention group from 12- to 18-months (+1.2%)[[31](#_ENREF_31)] and small changes in weight among the control group (approx ±1%).[[15-18](#_ENREF_15)] Thus, we expect that weight loss from baseline to 18-months follow-up, expressed as percent of initial body weight, will be at least 5% greater in the intervention group compared to the usual care group**.** Assuming a standard deviation of change of 8.5%[[16](#_ENREF_16)] and allowing 25% attrition at 18-months,[[32](#_ENREF_32)] 80 women per group (160 participants in total) will be needed to detect this minimum difference in weight loss between groups with 90% power and a type I error of 5% (two-tailed).

### Power for secondary endpoints

With a sample size of 80 per group we will have at least 80% power to detect clinically meaningful between-group differences for physical activity, energy intake, body composition, waist circumference, leptin, adiponectin, quality of life and body image, and between 50% to 80% power for the remaining secondary outcomes.[[16](#_ENREF_16), [30](#_ENREF_30), [33-39](#_ENREF_33)]

## Early stopping

There are no safety endpoints. No criteria for early study termination.

## Analytical plan

### 8.3.1 Statistical analyses for primary outcomes

Data analysis will be performed using SAS 9.2. Repeated measures regression model, using linear mixed model will be fitted, for the primary outcome (percent of initial body weight lost), including main effects of group and time and the interaction of group by time. The models will use baseline weight as a covariate to reduce the residual standard error and account for regression to the mean. Potential confounding variables such as stage of disease, menopausal status, treatment and pre-diagnosis weight will be examined to determine whether they are associated with the outcome and if so, will be included as covariates in the model. Statistical significance will be set at p < 0.05 (two-tailed).

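### Extra covariates in the primary model are picked by their association with the trial's own outcome, from an open list and with no stated criterion, so the model is not fixed before outcomes are seen

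*Protocol*

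**What the plan says.** Section 8.3.1 specifies a repeated-measures linear mixed model for percent of initial body weight lost, "including main effects of group and time and the interaction of group by time". Baseline weight always enters: "The models will use baseline weight as a covariate to reduce the residual standard error and account for regression to the mean". These parts are settled in advance.

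The rest of the adjustment is not. The rule for any further variable is that candidates "will be examined to determine whether they are associated with the outcome and if so, will be included as covariates in the model". Who the candidates are is indicated only by four examples: "Potential confounding variables such as stage of disease, menopausal status, treatment and pre-diagnosis weight". The paragraph ends with the general significance level: "Statistical significance will be set at p < 0.05 (two-tailed".

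Section 8.3.2 applies similar models to each secondary outcome. Section 8.3.3 varies the missing-data assumptions and the cut-points for activity and energy intake, but not the covariate set. Section 8.4 schedules separate analyses of the 6-month and 12-month outcomes once each follow-up is complete.

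**The concern.** Three features combine. The four named variables are examples, so the candidate list has no end. Association is undefined: the text gives no cut-off for this step and does not say whether candidates are screened singly or jointly, at which time point, or with the arms pooled. And inclusion depends on the trial's own outcome data. No other section closes the rule, and no model with a fixed covariate set is named as a reference.

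Two analysts following the text could therefore report different primary estimates and p-values, and a reader could not tell whether the choice was influenced by the result. The staged analyses add to this, because nothing says that the set used at 6 months carries over to 12 and 18 months.

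The rationale is also weak. In a randomised comparison, baseline imbalance arises by chance. Adjustment mainly serves precision, and prognostic variables can be named beforehand.

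**Working it through.** **1. The plan's own sample size.** The covariate rule does not enter this calculation, which supplies the setting for the simulation. Inputs from the section on power for primary endpoints: a difference that "will be at least 5% greater in the intervention group compared to the usual care group" (5 points); "Assuming a standard deviation of change of 8.5" percent; 25% attrition; 90% power; two-sided 5%.

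- n per arm = 2 × (1.960 + 1.282)² × 8.5² / 5² = 2 × 10.51 × 2.89 = 60.7, so 61.
- With attrition: 61 / 0.75 = 81.3, so 82, against 80 stated.
- Completers under the plan: 80 × 0.75 = 60 per arm. SE of the difference = 8.5 × √(2/60) = 1.55. Power = Φ(5/1.55 − 1.96) = 0.897.

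The stated figure reproduces closely enough.

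**2. Simulation set-up.** One time point, 60 completers per arm, outcome SD 8.5, no true effect. There are K independent standard normal candidates, each correlating r with the outcome. K and r are assumptions, since the protocol gives neither. K = 4 (4,000 trials per setting) gives 2⁴ = 16 subsets; K = 6 (2,000 trials per setting) gives 2⁶ = 64.

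**3. A mechanical rule.** Each candidate is kept if its correlation with the outcome has p < 0.05, or alternatively p < 0.20.

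| K, r | Type I error, selected | Type I error, all candidates fixed |
|---|---|---|
| 4, 0 | 4.8–5.0% | 5.1–5.2% |
| 4, 0.2 | 5.2% | 5.2% |
| 4, 0.3 | 4.9–5.2% | 4.9–5.1% |
| 6, 0.2 | 5.3–6.0% | 5.4–6.0% |

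The Monte Carlo standard error at 2,000 trials is √(0.05 × 0.95/2000) = 0.5 points. The 6.0% appears equally with the fixed set, so it is no sign of harm from selection.

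Precision is also recovered. With selected covariates the SD of the treatment estimate is about 1.44 at r = 0.2 and 1.26 at r = 0.3, against 1.53 unadjusted. For full adjustment, theory gives 1.55 × √(1 − 4 × 0.04) = 1.42 and 1.55 × √(1 − 4 × 0.09) = 1.24.

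**4. The room for choice.** Spread is the largest minus the smallest treatment estimate across all subsets in one trial.

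| K, r | Mean spread (points) | 90th percentile | Type I error if the best subset is always taken |
|---|---|---|---|
| 4, 0 | 0.4 | 0.7 | 6.5% |
| 4, 0.2 | 1.0 | 1.6 | 9.5–9.9% |
| 4, 0.3 | 1.5 | 2.3 | 13% (14% in a separate run) |
| 6, 0.2 | 1.5 | 2.2–2.3 | 14–16% |

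Against the 5-point target, mean spreads of 0.4, 1.0 and 1.5 are 8%, 20% and 30%. The last column is free choice on the treatment p-value, which section 8.3.1 does not propose.

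**The case against.** The strongest reply is that the stated rule does no measurable harm: selecting on association with the outcome, mechanically applied, keeps the type I error and gains the same precision as a fixed set. That stands. A reader might infer that the rule itself inflates error, or that adjustment helps only if fixed beforehand; step 3 shows neither. The best-subset figures likewise do not describe the plan.

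It can also be said that list and cut-off belong in an analysis plan, which may exist but is not shown. This stands only in part. The protocol does not defer; it states a data-driven rule for its primary model.

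The p < 0.05 in the next sentence might be read as the cut-off, but it is given as the general significance level and not tied to screening. One repeated-measures model would naturally carry one covariate set, so separate selection at each visit is a possibility left open, not something stated.

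Two stronger readings fail:

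- *Loss of women through missing treatment data.* Section 5.6.6 says "Collection of this data will be dependent on adequate resources for study staff to abstract this data from hospital medical records", but this concerns record details such as cycles and agents. Treatments received and menopausal status at diagnosis come from the first telephone interview (5.6.4), and pre-diagnosis weight from the body composition assessment (5.6.1). Section 5.6 requires both assessments before randomisation. Stage is an eligibility item.
- *Selection by an unblinded analyst.* The text does not say so. Association can be examined with arms pooled and without group codes.

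**Conclusion.** The point holds in a limited form. The group and time terms and baseline weight are fixed; the remaining covariates are not, because list and criterion are open and inclusion depends on outcome data. The primary model is therefore not determined before outcomes are seen.

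The exposure is a spread in the treatment estimate of about 0.4 to 1.5 percentage points on average for four candidates, for assumed correlations of 0 to 0.3. Best-subset choice would give a type I error of about 6% to 14%, as an illustration of the latitude. With more candidates both grow. The figures rest on independent covariates, one time point instead of the mixed model, and 60 completers per arm. They do not show that the stated procedure is biased or that the trial is invalid. This should be corrected, and the correction is easy.

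**What to change.** Replace the selection sentence in section 8.3.1 with a closed set, named before outcome data are examined and included whatever association is observed. One such set is baseline weight, disease stage, menopausal status at diagnosis, treatment received as recorded at the baseline interview (with its coding stated), and self-reported pre-diagnosis weight. Use it unchanged at 6, 12 and 18 months, and report the model with baseline weight only as a sensitivity analysis. Making the baseline-weight-only model primary and the adjusted one a sensitivity analysis would close the gap equally well.

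The cost is a sentence or two and a few degrees of freedom. With stage in three categories and treatment as a binary variable, the additional covariates use 2 + 1 + 1 + 1 = 5, among about 120 women. Sample size and nominal alpha do not change, and no new data are needed.

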### 8.3.2 Statistical analyses for secondary outcomes

Similar models will be performed for each secondary outcome, using the baseline value of the outcome as a covariate.

### 8.3.3 Sensitivity analyses

Sensitivity analyses will be conducted using different assumptions for handling missing data. Sensitivity analyses for secondary outcomes will include using different cut-points for device-measured physical activity; different cut-points for over- and under-estimating energy intake.

### 8.3.4 Subgroup analyses

Further analyses will be performed to compare the following groups:

- Those completing at least 75% of intervention calls
- Those with pre-existing type 2 diabetes or elevated cardio-metabolic biomarkers (e.g. LDL-cholesterol, blood pressure) at baseline

### 8.3.5 Exploratory analyses

Exploratory analyses will be conducted to determine whether there is moderation or mediation of intervention effects using previously established methods. Moderator analysis will determine whether intervention effects differ across demographic (e.g. age, menopausal status) and breast cancer (e.g. chemotherapy treatment, fear of cancer recurrence) characteristics and will be performed by considering the statistical significance of an interaction between a potential moderator and the intervention using a Wald test. Mediator analysis will determine whether theoretically-driven constructs and mechanisms for behaviour change do in fact mediate the intervention effects. Potential mediators will be assessed using path analysis. Point estimates and bootstrap confidence intervals of path coefficients and the product of the mediated path coefficients will be used to determine the potency, certainty and direction of any mediation effect [[40](#_ENREF_40)].

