## Hypotheses

1. Weight loss from baseline to 12-months follow-up, expressed as percent of initial body weight, will be at least 5% greater in the intervention group compared to the usual care group.

1b. Participants in the intervention group will report significantly greater improvements in all secondary outcomes (body composition, physical activity, diet, metabolic and genomic biomarkers, blood pressure, and patient reported outcomes) compared to the usual care group at the end of intervention (12-months).

1c. Differences observed between intervention and usual care groups for primary and secondary outcomes at 12-months will be maintained at 18-months follow-up.

2. The intervention will be cost-effective (less than $50,000 per disability-adjusted life year), compared to usual care.

Aims 3 and 4 are exploratory and not hypothesis testing.

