## Study design

**Design:** This is a randomized controlled trial, with participants randomly allocated to one of two groups: 12-month weight loss support intervention or usual care.

**Data Collection:** Data collection points occur at baseline, 6-months (short-term), 12-months (end-of-intervention) and 18-months (maintenance post-intervention).

See Figure 1 for an overview of the study design

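### Section 8.3.5 concludes more than a product-of-paths interval can show: the product can be non-zero without mediation, so the conclusion should be stated as conditional

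*Protocol*

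**What the plan says.** Section 8.3.5 of the protocol plans a path analysis of potential mediators. It states the purpose as: "Mediator analysis will determine whether theoretically-driven constructs and mechanisms for behaviour change do in fact mediate the intervention effects". The evidence is to be as follows: "Point estimates and bootstrap confidence intervals of path coefficients and the product of the mediated path coefficients will be used to determine the potency", and the same sentence adds the certainty and direction of any mediation effect.

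Section 5.6.5 describes the candidates, namely social-cognitive constructs together with sleep and depression, "which will be examined to assess whether they mediate or moderate the relationship between the intervention and the primary and secondary outcomes". One listed instrument is "Satisfaction with diet and physical activity outcomes".

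On timing, Section 3.3 says: "Data collection points occur at baseline, 6-months (short-term), 12-months (end-of-intervention) and 18-months". The assessment table in Section 5.6 places the questionnaire and the weight measurement at the same visits. On adjustment, Section 8.3.1 says of the primary model: "Potential confounding variables such as stage of disease, menopausal status, treatment and pre-diagnosis weight will be examined". Section 8.3.5 names no covariates and no time order for the mediation paths. The sensitivity analyses in Section 8.3.3 deal with missing data and cut-points, not with mediation.

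Section 3.2 gives the status of this work: "Aims 3 and 4 are exploratory and not hypothesis testing".

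**The concern.** The stated conclusion does not follow from the stated statistic. An interval for the product that excludes zero shows two things: the arm shifts the construct, and the construct is associated with the outcome given arm. Randomisation makes the first causal. It does nothing for the second, because nobody is randomised to a level of the construct.

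Two structures give a non-zero product with no mediation:

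- **The construct follows weight loss.** Satisfaction with outcomes, sleep and depression could plausibly improve because weight has fallen.
- **A shared cause.** The coaching shifts the construct, and an unmeasured trait such as motivation drives both the construct and weight.

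Aim 3 is meant to explain how the intervention worked. If such constructs are reported as established mechanisms, with certainty and direction, readers may build later programmes around consequences or markers of weight loss.

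**Working it through.** **Inputs from the protocol (Section 8.1.1).** Difference 5 percentage points, SD of change 8.5, 25% attrition, 90% power, two-sided 5%, 80 per group.

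**Reproducing the plan's figure.** Per arm, n = 2 × (1.96 + 1.282)² × (8.5/5)² = 60.7, so 61. Allowing for attrition, 61/0.75 = 81.3, so 82, which is within 2 of the stated 80. With 80 × 0.75 = 60 per arm, power is 89.7%. The standardised effect on weight is 5/8.5 = 0.59 SD. The protocol gives no figure for mediation, so these values only set the scale of the simulation.

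**Assumed, not in the documents.** The construct's correlation with weight within arm; the arm's effect on the construct; and a 95% percentile bootstrap interval, since Section 8.3.5 states no level.

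**Statistic.** X is arm, M the construct, Y weight change (SD units, signed so that a larger value is more loss). a = mean M in the intervention arm minus mean M in usual care. b = pooled within-arm slope of Y on M. The product is a × b. The true effect of M on Y is zero throughout.

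**What the product estimates when there is no mediation.**

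- *Construct follows weight:* M = rY + √(1 − r²) × noise. Then a = 0.59r, b = r and a × b = 0.59r². At r = 0.3 this is 0.05; at r = 0.5 it is 0.15, which is r² = 25% of the whole intervention effect.
- *Shared cause with residual correlation r, arm shift 0.5 SD:* a × b = 0.5r, so 0.10, 0.15 and 0.25 at r = 0.2, 0.3 and 0.5.

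**How often the 95% interval excludes zero, 60 per arm** (400 or 1,000 trials per setting; ranges span repeated runs):

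| Structure, no true mediation | Correlation | Rate |
|---|---|---|
| Construct follows weight | 0.1 | 0.7% |
| | 0.2 | 5% |
| | 0.3 | 14-17% |
| | 0.4 | 24% |
| | 0.5 | 35-39% |
| Shared cause, arm shift 0.5 SD | 0.2 | 45-46% |
| | 0.3 | 69-74% |
| | 0.4-0.5 | 77-79% |
| Shared cause, arm shift 0.3 SD | 0.2 / 0.3 / 0.5 | 20% / 35% / 41% |
| Shared cause, arm shift 0.8 SD | 0.2 / 0.3 / 0.5 | 61% / 92% / 99% |
| Shared cause, arm does not move construct | 0.2 / 0.3 / 0.5 | 3% / 5% / 7% |
| No association of M with Y | 0 | 0-4% |

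At 80 per arm the rates for a construct that follows weight rise to 18% (0.3) and 45% (0.5). More data sharpen the wrong answer.

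**Cross-check.** Once b is reliably non-zero, the rate should approach the power to detect a. For a = 0.5 SD: 0.5 × √(60/2) = 2.74, and Φ(2.74 − 1.96) = 78%, matching the plateau. For a construct that follows weight at r = 0.5: a = 0.29, 0.29 × √30 = 1.61, and Φ(1.61 − 1.96) = 36%, matching 35-39%. In these settings the interval mainly reports whether the arm moved the construct.

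**What possible remedies do.**

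- Adjusting for a shared cause that has been measured (arm shift 0.5 SD, correlation 0.3) cuts 69% to 6%.
- Taking the 6-month construct and 12-month weight, adjusted for 6-month weight, cuts the rate for a construct that follows weight to about 1-2% (correlation 0.8 assumed between visits). In further simulations, however, the same rule found true same-visit mediation in only 8-12% of trials, against 77-80% for the same-visit product. It still excluded zero in 14-28% under a shared cause.

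**The case against.** The strongest reply is that the protocol never presents this as confirmatory. Section 3.2 sets aims 3 and 4 apart from hypothesis testing, Section 8.3.5 is headed as exploratory, and no error rate, confidence level or rule for declaring a mediator is given. This stands. A reader might infer that a 5% error rate is breached, but the documents set none for this aim.

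A reader might also infer that the plan commits to unadjusted models of construct and weight at the same visit. It does not. It is silent on order and covariates, path analysis can handle both, the 6-, 12- and 18-month visits permit a lagged model, and an analysis plan that is not shown may fix these details. That silence is not the finding.

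Nor do the documents support saying that constructs in general will be falsely named mediators. Most of the list (self-efficacy, self-regulation, social support, outcome expectancy) consists of theorised antecedents of behaviour. That satisfaction, sleep or depression follow weight loss is a plausible judgement and not a fact in the protocol. The excess also depends on assumed correlations and arm shifts.

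What the reply does not remove is the sentence itself. Exploratory status does not turn an association into a demonstrated mechanism, and Section 8.3.5 states that conclusion in its own words.

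**Conclusion.** The point holds as a minor one about what Section 8.3.5 says it can conclude. The product interval cannot determine whether a construct mediates. It estimates an indirect effect only if the construct precedes the outcome and no unmeasured cause is shared between them, and Section 8.3.5 states neither condition.

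The possible size is material but conditional. With 60 per arm and no true mediation, the rate is 14-17% to 35-39% for a construct that follows weight at assumed correlations of 0.3 to 0.5, and 45-79% for an assumed 0.5 SD arm shift with shared-cause correlations of 0.2 to 0.5. It is about 3-7% when the arm does not move the construct, and at most 5% when a construct follows weight at a correlation of 0.2 or less. It would go too far to say that the answer to aim 3 will be wrong, because the documents do not show which of these settings applies. The primary analysis and the sample size are unaffected.

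**What to change.** In Section 8.3.5:

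1. Replace the sentence on what the mediator analysis will determine with: *Mediator analysis will estimate indirect effects, assuming no unmeasured mediator-outcome confounding and that the mediator precedes the outcome.*
2. Adjust the mediator-to-outcome path for the baseline value of the mediator, baseline weight and the baseline factors named in Section 8.3.1.
3. For each indirect effect, report the residual mediator-outcome correlation that would bring it to zero.
4. As a sensitivity analysis for time order, present the 6-month mediator with 12-month weight, both with and without adjustment for 6-month weight.

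Item 4 should not become the only rule. Section 5.3.1 places 16 of the 22 calls in the first 6 months, so mediation may act early. Adjusting for 6-month weight then removes most of the power, and it does not remove shared-cause bias.

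The cost is a revised paragraph and a little programming, with no new data. The conclusions on aim 3 will be less definite.
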